### Intervention procedure

#### Vitamin D intervention

Patients in the VG or VEG group will receive one tablet of vitamin D_3_ supplement (1000 IU/day, Nature Made, Otsuka Pharmaceutical Co, Ltd, Tokyo, Japan) immediately after meals to enhance absorption based on the guideline of Institute of Medicine for Vitamin D recommended [26], and patients in the EG or CG group will receive an identical appearance shape and color placebo as the vitamin D_3_ supplement every day for 3 months.

#### Exercise intervention

Patients in the EG or VEG group will perform a 1-h progressively increasing aerobic exercise (cycling, running, or rowing) at 60–80% of maximal heart rate 3 times a week for 3 months [25], and this will be supervised by a qualified trainer who is knowledgeable of the study protocol and procedures. Polar monitor will be used to monitor heart rate during exercise, and the compliance (exercise time and intensity) with each protocol will be recorded. Participants will warm up during the first 5 min on a treadmill at 50–60% of maximal heart rate and subsequently follow the exercise protocol assigned to them, with a 5–10-min recovery exercise at 40–50% of maximal heart rate, which comprises walking and stretching exercise.

### Patient and public involvement

Patients will not be involved in recruitment of participants or conduct of the study. The results of this study will feedback and disseminate to all of participants.

### Data collection

#### Outcome measures and measurement procedures

A full list of measurable outcomes is presented in Table 1. Participants will be assessed at baseline, at the end of intervention, and 3 months after the intervention (Table 2).

**Table 1 Tab1:** Summary of outcome measures

Outcomes	Item	Device
**Primary outcomes**		
Insulin sensitivity and insulin secretion	The Matsuda index, the insulinogenic index, HOMA-IR, HOMA-β	OGTT
		Fasting blood measurements
Vitamin D level	Serum 25(OH)D, 1,25(OH)_2_D	Fasting blood measurements
**Secondary outcomes**		
Body composition	Percent body fat, muscle mass	DXA
	Waist circumference	Standard tape
Metabolic indices	Fasting glucose (G_0_), fasting insulin (I_0_), HbA1c, triglyceride, cholesterol, low-density lipoprotein, and high-density lipoprotein	Fasting blood measurements
Ankle-brachial index	Blood pressure, ABI, baPWV	Validated automatic device
Physical fitness factors	Peak oxygen uptake, maximal heart rate	Cycle ergometer
	Hand grip strength	Hand grip dynamometer

*HOMA* Homeostatic model assessment, *IR* Insulin resistance, *25(OH)D* 25-hydroxyvitamin D, *1,25(OH)*_*2*_*D* 1,25-Dihydroxyvitamin D, *OGTT* Oral glucose tolerance test, *DXA* Dual-energy X-ray absorptiometry, *HbA1c* Glycated hemoglobin, *ABI* Ankle-brachial index

**Table 2 Tab2:** Example template of recommended content for the schedule of enrolment, interventions, and assessments

	Study period				
Timepoint	Enrolment and baseline allocation 0 week	Intervention 1–12 weeks	Post-intervention 13 weeks	Follow-up 13–24 weeks	Close-out 25 weeks
**Enrolment**					
Eligibility screen	X				
Informed consent	X				
Randomization and allocation	X				
**Exercise/vitamin D intervention**		X			
**Assessment**					
Blood parameter tests	X		X	X	
Body composition	X		X	X	
Ankle-brachial index	X		X	X	
Physical fitness factors	X		X	X	

Analysis of blood samples is as follows: a standard 75-g oral glucose tolerance test (OGTT) will be performed between 0830 and 1100 after a 12-h overnight fast, and venous blood samples will be collected in Venoject-II AutoSep tubes at time points 0, 30, 60, 90, and 120 min to determine the plasma glucose and serum insulin levels. Fasting serum sample will be used to measure the levels of 25(OH)D, 1,25(OH)_2_D, calcium, fasting glucose (*G*_0_), fasting insulin (*I*_0_), HbA1c, triglyceride, cholesterol, low-density lipoprotein, and high-density lipoprotein.

Primary outcomes are as follows: changes in insulin sensitivity and secretion.

Fasting blood glucose and insulin will be used to calculate the insulin resistance index (Homeostatic Model Assessment of Insulin Resistance [HOMA-IR]) and β cell secretion index as follows: HOMA-IR = *G*_0_ × *I*_0_/22.5 and HOMA-β = 20 × *I*_0_/(*G*_0_ – 3.5).

Insulin sensitivity estimated using the Matsuda index of insulin sensitivity during the OGTT will be calculated as follows: 1000/square root of ([*G*_0_ × *I*_0_]) × (mean OGTT glucose concentration × mean OGTT insulin concentration) [27]. Early phase of insulin secretion will be estimated using the insulinogenic index as follows: *I*_30_–*I*_0_/*G*_30_ – *G*_0_ (△I30/△G30), where *I*_30_ and *G*_30_ represent insulin and glucose values at 30 min during the OGTT, respectively [28]. The increments in the area under the curves during the complete 120-min period of the OGTT will be calculated using the trapezoid rule to assess the total changes in glucose and insulin levels [22].

Secondary outcomes are as follows: changes in anthropometry, metabolic indices, ankle-brachial index, and physical fitness factors

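### The written formula for the Matsuda index, a primary outcome, closes the square root too early, so the index rises with OGTT glucose and insulin

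*Protocol article*

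**What the plan says.** In the protocol article, Table 1 lists four indices as primary outcomes for insulin sensitivity and secretion: "The Matsuda index, the insulinogenic index, HOMA-IR, HOMA-β". The text under *Outcome measures and measurement procedures*, after Table 2, repeats the role: "Primary outcomes are as follows: changes in insulin sensitivity and secretion".

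The same text introduces the formula with "Insulin sensitivity estimated using the Matsuda index of insulin sensitivity during the OGTT will be calculated as follows" and gives it as "1000/square root of ([*G*_0_ × *I*_0_]) × (mean OGTT glucose concentration × mean OGTT insulin concentration"), followed by reference 27. Glucose and insulin are sampled "at time points 0, 30, 60, 90, and 120 min to determine the plasma glucose and serum insulin levels", and the two OGTT means would come from these samples. The companion resistance index is "HOMA-IR = *G*_0_ × *I*_0_/22.5".

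The Matsuda formula is not restated anywhere else in the article.

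**The concern.** The bracket under the root opens and closes around the fasting product. The OGTT product stands in its own bracket as a multiplier, and nothing places it in the denominator. A sensitivity index should fall as a patient becomes more resistant. This one, taken literally, grows in direct proportion to OGTT glucose and insulin.

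Of the four primary indices, HOMA-IR and HOMA-β use fasting values only, and the insulinogenic index measures secretion. The Matsuda index is therefore the only primary measure of sensitivity taken from the OGTT. The abstract and the Discussion base the trial's claim to be first on insulin resistance assessed by OGTT. An analyst or replicator who programs the line as printed could report an effect on that measure with the wrong sign.

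**Working it through.** The protocol gives no worked value for this index, so there is no figure to reproduce. The check compares three readings of the formula. Write F = G0 × I0 (fasting product) and M = mean OGTT glucose × mean OGTT insulin.

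- Reading A, as printed and evaluated left to right: 1000/√F × M
- Reading B, means in the denominator but outside the root: 1000/(√F × M)
- Reading C, all four terms under one root: 1000/√(F × M)

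**Algebra, no inputs needed.** Suppose F and M both rise by a factor k > 1. HOMA-IR = F/22.5 changes by k. Reading A changes by k × k^(−1/2) = k^(+1/2), so it rises. Reading B changes by k^(−3/2) and reading C by k^(−1), so both fall. More generally, A rises whenever M grows proportionally more than √F. If only F rises, A falls.

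**Illustration.** The profiles are assumptions, not protocol figures, with glucose in mmol/L and insulin in mU/L. The less resistant profile has G0 6, I0 8, mean glucose 9 and mean insulin 40, so F = 48 and M = 360. The worse profile multiplies glucose by 1.25 and insulin by 1.5, so each worsened product grows by 1.25 × 1.5 = 1.875, to F = 90 and M = 675.

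| Profile | F | M | HOMA-IR | A (as printed) | B | C |
|---|---|---|---|---|---|---|
| Less resistant | 48 | 360 | 2.13 | 51,962 | 0.401 | 7.61 |
| Fasting and OGTT worse | 90 | 675 | 4.00 | 71,151 (+37%) | 0.156 (−61%) | 4.06 (−47%) |
| OGTT only worse | 48 | 675 | 2.13 | 97,428 (+88%) | 0.214 (−47%) | 5.56 (−27%) |
| Fasting only worse | 90 | 360 | 4.00 | 37,947 (−27%) | 0.293 (−27%) | 5.56 (−27%) |

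For the second row, A = 1000/√90 × 675 = 71,151 and C = 1000/√(90 × 675) = 4.06. The ratios match the algebra: √1.875 = 1.369 for A and 1/1.875 = 0.533 for C.

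The table shows three things:

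- Reading A has the wrong direction in two of the three worsening patterns and the right direction in the third.
- Reading B always has the right direction but is a different index. The same worsening of the OGTT product costs 47% under B and 27% under C, because M enters with power −1 instead of −1/2.
- Reading C weights the fasting and OGTT products equally and falls in every pattern.

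The percentage changes do not depend on the constant 1000 or on the units, since both cancel.

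**The case against.** The strongest reply is that this is a bracketing slip with an obvious intention. The double bracket around the fasting product is redundant unless the outer one was meant to run on over the whole expression. The sentence names the index, calls it insulin sensitivity and cites a source. The insulinogenic index that follows is bracketed just as loosely. All this is fair evidence of intent. However, the insulinogenic index carries a gloss as a ratio of 30-minute increments that settles its meaning, and the Matsuda formula has none. The intention also does not correct the printed definition of a primary outcome.

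A second reply is that the error would be noticed. In the less resistant profile, reading A gives 51,962 where reading C gives 7.61, and HOMA-IR is written unambiguously in the same text as a check on direction. This lowers the practical risk of reading A. It protects less against reading B, which agrees with HOMA-IR in direction.

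A reader might infer three stronger things that the document does not support:

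- **Any benefit would appear as harm.** It would not: the printed index still falls when only fasting values worsen, and the largest reversals come from examples that hold fasting values fixed.
- **The trial's results are or will be computed wrongly.** Nothing shows that the analysis program uses the printed line; it may already follow the cited source.
- **The units or the constant are also in error.** A journal article may leave assay units to the full protocol, and the constant could be checked only against a source not at hand. Neither bears on the direction of the index.

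**Conclusion.** The formula is wrong as written. The printed Matsuda index rises in proportion to the OGTT product and moves in the wrong direction whenever that product changes proportionally more than √(G0 × I0), including when fasting and OGTT products worsen by the same factor. In the assumed profiles with both worsening, it rises 37% where the all-under-root form falls 47%. The sizes rest on those assumed values; the direction rests on algebra alone. The alternative reading, with the means in the denominator outside the root, gets the direction right but squares the weight of the OGTT product relative to the all-under-root form (power −1 instead of −1/2).

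This is an error in the written definition of one of several primary indices. It is not evidence of a wrong computation, and it does not touch sampling, conduct or sample size. It should be corrected because a primary outcome's formula should not contradict its own name.

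**What to change.** Replace the formula with 1000/√[(G0 × I0) × (mean OGTT glucose × mean OGTT insulin)], with all four terms visibly under one root. Before unblinding, run the analysis program on one worked patient and confirm that it reproduces a hand calculation of this form, and that the index falls when the OGTT values are raised.

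The cost is one line of text and one program check. The five planned OGTT samples already supply every term, so no data collection changes.

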#### Anthropometry

Height and body mass will be measured with the participants in light clothing and barefoot. Body mass index will be calculated by dividing the body mass in kilograms by the square of height in meters (kg/m^2^). Waist circumference will be measured to the nearest 0.1 cm at the umbilical region using an inelastic measuring tape at the end of normal expiration. DXA is used to measure percent body fat and muscle mass (Hologic QDR-4500, DXA Scanner, Hologic Inc., Waltham, MA, USA) by a recognized technologist.

#### Ankle-brachial index

Blood pressure and brachial-ankle pulse wave velocity (baPWV) will be measured after the participant had rested supine for at least 5 min using a validated automatic device (BP-203RPE, II form PWV/ABI, Omron-Colin, Japan) in the brachial and ankle arteries. An oscillometric method will be used, and its cuffs have sensors that transmit data to the device. The baPWV will be calculated by dividing the distance from the aortic valve to the ankle artery by the sum of the time between the aortic valve closing sound and the notch of the brachial pulse wave and the time between the increase in the brachial pulse wave and that of the ankle pulse wave. The ankle-brachial index will be calculated by dividing the highest value obtained at each ankle by the highest of the arm values [29].

#### Physical fitness factors

Peak oxygen uptake (VO_2peak_) will be measured using a maximal graded exercise test using a cycle ergometer (MetaMax 3B, Cortex, Germany). The graded cycle exercise will begin at a workload of 45–90 W, which is subsequently increased by 15 W/min until the subject could not maintain the required pedaling frequency of 60 rpm. During the progressive exercise test, the expired gas of subjects will be collected, and the rates of oxygen consumption and carbon dioxide production will be measured and averaged over 30-s intervals using an automated gas analyzing system. The highest recorded value of VO_2_ and heart rate during the exercise test will be quantified as the VO_2peak_ (mL·kg^−1^·min^−1^) and maximal heart rate (bpm) [30]. Vigorous activities and alcohol and caffeinated beverages will be prohibited 2 days before the test.

Handgrip strength will be measured using a hand grip dynamometer (HK6800-WL, Shenzhen, China) in units of kilograms. Participants will be instructed to complete two handgrip contraction trials bilaterally, alternating hands between trials. The highest values obtained using each hand were considered the right-hand and left-hand grip strength scores [30]. The mean value of the two maximal grip strength scores will be used.

#### Sunlight exposure

Participants will be instructed to record their outdoor activity time and exposed areas of the skin from 9 am to 5 pm for 7 consecutive days in a week using a questionnaire every month. A score to estimate the mean weekly sunlight exposure will be calculated, and additional details were published elsewhere [31].

#### International Physical Activity Questionnaire

Daily physical activity except for the exercise program will be assessed using the International Physical Activity Questionnaire monthly and expressed as metabolic equivalent minutes per week. It refers to the preceding 7 days and instructs participants to report the number of days, hours, and minutes spent on vigorous activity, such as aerobics, or moderate activity, such as carrying light loads [32].

### Follow-up visits

Participants will be scheduled for their follow-up visits during the last week of their treatment assessing all procedures performed during baseline assessment including blood pressure measurement, anthropometry, OGTT, DXA, physical activity and dietary assessment using structured questionnaires.

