**Methods and analysis:**

We propose a 3-month randomized controlled trial among 60 T2DM patients aged 40–65, newly diagnosed with T2DM ≤ 1 year, and with stable HbA1c level (≤ 8.0%) in the past 3 months. The participants will be randomly allocated to the vitamin D group, vitamin D combined with exercise training group, exercise training group, and control group (CG) using a computer-generated random number sequence. At baseline, participants will undergo a medical review, anthropometric measurements, dual X-ray absorptiometry, a 75-g oral glucose tolerance test (OGTT), ankle-brachial index measurements, and physical fitness measurements and will complete related lifestyle questionnaires. Fasting blood lipid and glucose levels were also measured. In a 3-month intervention period, vitamin D intervention group will receive a dose of 1000 IU daily; exercise group will perform a 1-h endurance exercise 3 times per week (maximal heart rate, 60–80%), and the control group will receive apparently identical tablets. Additionally, all participants will be advised to maintain their normal diet and physical activities during the intervention. All measurements will be repeated at 3-month follow-up after the intervention with the primary outcome measure expressed as a change from baseline in insulin sensitivity and secretion. Secondary outcome measures will compare the changes in anthropometry, ankle-brachial index, and physical fitness factors (e.g., peak oxygen uptake, hand grip strength). Data will be managed and analyzed using the Statistical Package for the Social Sciences.

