Documented evidence demonstrated that physical inactivity and obesity are two major risk factor for the development of T2DM; exercise intervention, where aerobic or resistance training or a combination, can exert many beneficial effects, such as increase fat oxidations, in the prevention and treatment of T2DM [18]. Exercise training not only increases energy consumption and reduces the accumulation of lipids in insulin-sensitive tissue such as the skeletal muscle [19] but also promotes glucose transportor-4 (GLUT-4) translocation and glucose uptake in skeletal muscle cells by activating AMP-activated protein kinase (AMPK) and downstream proteins of insulin-transmitting signals in skeletal muscle cells [20]. Additionally, recent studies have shown that exercise may also be involved in the regulation of vitamin D, which can increase VDR expression in skeletal muscle tissue and serum 25(OH)D levels [21–23]. Prior evidence suggested that in addition to regulating Ca^2+^ levels, vitamin D supplementation can directly upregulate the AMPK-GLUT-4 signaling pathway through VDR related (phosphorylated ERK1/2 and Mnk1) expression to increase glucose utilization and participate in exercise pathways of glucose utilization pathways [23]. These results suggested that vitamin D supplementation combined with exercise intervention may have a synergistic effect on the improvement of IR by activating different glucose utilization pathways. However, studies investigating the synergistic effect of vitamin D supplementation combined with exercise training intervention on IR in T2DM patients are relatively few [24].

In summary, this study aimed to (1) examine the effect of vitamin D supplementation on IR and (2) determine the synergistic effect of vitamin D supplementation combined with exercise training intervention on IR in Chinese T2DM patients with vitamin D deficiency by a randomized controlled trial.

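### The protocol gives conflicting times for the post-treatment OGTT, and on one of them the exercise arms are tested while still training, with no stated exercise-free interval

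*Protocol article*

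**What the plan says.** The protocol article times the repeat measurements in four places:

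- **Follow-up visits:** "Participants will be scheduled for their follow-up visits during the last week of their treatment". The OGTT is among the procedures listed.
- **Table 2:** the columns read "Intervention 1–12 weeks" and "Post-intervention 13 weeks", and blood tests are ticked in the second.
- **Outcome measures and measurement procedures:** "Participants will be assessed at baseline, at the end of intervention, and 3 months after the intervention".
- **Abstract:** "All measurements will be repeated at 3-month follow-up after the intervention with the primary outcome measure expressed as a change from baseline".

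On preparation, the article says that "a standard 75-g oral glucose tolerance test (OGTT) will be performed between 0830 and 1100 after a 12-h overnight fast" and adds nothing about prior exercise. For the peak oxygen uptake test, a secondary outcome, it says "Vigorous activities and alcohol and caffeinated beverages will be prohibited 2 days before the test".

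Only EG and VEG have supervised sessions: 1 hour, three times a week, for 3 months (Exercise intervention). All four arms are told to leave their general activity unchanged (Randomization).

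**The concern.** The primary outcome is the change in insulin sensitivity and secretion, taken from the OGTT and the fasting sample. The Introduction attributes to exercise training a rise in muscle glucose uptake through AMPK and GLUT-4. If the OGTT is done during the training period, a session a day or two earlier could plausibly affect the indices as well as the 3 months of training. The control (CG) and vitamin D (VG) arms have no such session. Randomization does not remove a difference in measurement conditions that comes with the arm.

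The exercise contrasts would then combine a training effect and a last-bout effect in unknown proportions. The comparison with the later visit would be affected too, because no supervised session precedes that one. Since the text allows more than one timing, the interval could also vary between patients.

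**Working it through.** No figure in the plan bears on this point, so the check sets the timings side by side, works out the interval each implies, and traces which contrasts are affected.

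**1. Days from the last session to a morning OGTT.** The protocol gives three sessions a week but names no days. Assume sessions on days 1, 3 and 5, with the OGTT before any session that day.

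| OGTT in the last training week, on day | 1 | 2 | 3 | 4 | 5 | 6 | 7 |
|---|---|---|---|---|---|---|---|
| Days since last session | 3 | 1 | 2 | 1 | 2 | 1 | 2 |

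The gap is at most 2 days on 6 of 7 mornings (4 of 5 if only days 1–5 are used) and 1 day on 3 of 7. If sessions are bunched on days 1, 2 and 3, the gaps are 5, 1, 1, 1, 2, 3 and 4 days, so 4 of 7 mornings are within 2 days.

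Under Table 2, the last session is on day 5 of week 12 and week 13 runs from day 8 to day 14 on the same count. The gap is 8 − 5 = 3 to 14 − 5 = 9 days. With sessions on days 2, 4 and 6 it would be 8 − 6 = 2 to 14 − 6 = 8 days.

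At a visit 3 months after the intervention there is no recent supervised session.

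**2. Contrasts affected.** Let a last-bout effect shift the mean by *a* in EG and VEG and by 0 in CG and VG, on the scale analysed.

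| Contrast | Contribution of the shift |
|---|---|
| EG − CG | *a* − 0 = *a* |
| VEG − CG | *a* − 0 = *a* |
| VEG − VG | *a* − 0 = *a* |
| Exercise main effect, (EG + VEG)/2 − (CG + VG)/2 | *a* |
| VG − CG | 0 − 0 = 0 |
| VEG − EG | *a* − *a* = 0 |
| Interaction, (VEG − EG) − (VG − CG) | 0 − 0 = 0 |

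**3. Illustration only.** The documents give no value for *a*. Suppose there is no training effect and *a* is an assumed fraction of the SD of the outcome, present in every EG and VEG patient. With the planned 48 evaluable patients (24 v 24), the 1-df F test at 0.05 has 44 error degrees of freedom and noncentrality (*a*/2)² × 48.

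| Assumed *a* (SD) | Noncentrality | Rejection probability |
|---|---|---|
| 0.1 | 0.12 | 6% |
| 0.2 | 0.48 | 10% |
| 0.3 | 1.08 | 17% |
| 0.5 | 3.00 | 40% |

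The spread shows only that the result depends on the assumption. It is not an estimate of bias in this trial.

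**The case against.** Several objections carry weight.

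- **The last-week timing is not settled.** On Table 2 the interval is already 3–9 days for the day 1, 3, 5 calendar, beyond the 2-day rule used for the fitness test. This stands, and it is why the point is a contradiction to resolve. A reader might infer that the OGTT does fall in the training period; the documents do not establish that.
- **The acute effect is not in the documents.** The Introduction speaks of exercise training and gives no size or duration for a single bout. The 2-day interval comes from a rule for a different test. This stands: size and persistence are both assumed.
- **The stated aims are spared.** They are the vitamin D effect and the synergy with exercise, and a common shift cancels in the contrasts that carry them. This stands. However, the abstract and Discussion also promise the independent and combined effects of both interventions, and that needs the exercise contrasts.
- **A last-bout effect is part of exercise as delivered.** That is a legitimate target, but the article does not say it is the intended one.
- **The maximal cycle test might seem to add to the imbalance.** It does not, because all four arms do it. Its order relative to the OGTT is a matter of standardization.
- **A condensed article may omit OGTT instructions.** The full protocol may contain a rule, and if the two tests share a visit the fitness-test ban could protect the OGTT incidentally. This is possible. But the article does state an activity restriction for a secondary test, does not say whether supervised sessions count as vigorous, and does not say that the tests share a visit.

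**Conclusion.** The contradiction in timing is plain on the text and needs correction. The Follow-up visits section and Table 2 cannot both be followed, and the abstract leaves open whether the primary time point is the end of treatment or 3 months later.

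The consequence is conditional. If the last-week instruction is followed, most OGTT mornings fall within about 2 days of a session in EG and VEG (6 of 7 with evenly spaced sessions), with only a fast and a clock window stated as preparation. Any last-bout effect would then be inseparable from the training effect in EG−CG, VEG−CG, VEG−VG and the exercise main effect. On the week-13 timing the problem is much smaller, and 3 months after the intervention it is absent.

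The cancellation in VG−CG, VEG−EG and the interaction assumes the same shift in EG and VEG on the scale analysed. A reader might infer that the primary endpoint is contaminated throughout, or that the trial's false-positive rate is raised by a known amount. The documents support neither.

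**What to change.** 1. Reconcile the abstract, the outcome section, Table 2 and the Follow-up visits section to one post-treatment visit time, and name the primary time point.
2. Extend the existing 2-day restriction on vigorous activity to the OGTT and the fasting sample, in all arms and at all visits, and state that supervised sessions count.
3. As standardization, do the OGTT before the maximal cycle test.
4. Record the time since the last supervised session at each OGTT.

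If the sponsor wants the last bout included in the exercise effect, the protocol should say that this is the effect being estimated.

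The cost is protocol wording and visit booking, with no extra test or staff. The small downside is tighter scheduling of the post-treatment visit.
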